### Setting and population

The study setting is the Joint Surgery Unit of the Orthopedics Department at a hospital.

Patients on the surgical waiting list for THA will be invited to participate in the study after preoperative assessment. Men and women aged 18 years or older and scheduled for primary, single-side THA surgery at the Joint Surgery Unit are eligible for participation. Trial inclusion criteria are the following: participants must be able to read and understand Chinese, be willing to participate in a 6-month exercise intervention, and provide informed consent. Participants are ineligible if they meet one or more of the following exclusion criteria: (i) an unstable medical condition due to fracture, malignancy, infection, or THA failure; (ii) inability to provide informed consent due to mental disorder, dementia, or cognitive impairment that prevent completion of self-report surveys; (iii) co-existing conditions that would negate functional improvement with surgery and exercise (e.g., severe Parkinson disease, or hemiparesis); (iv) simultaneous bilateral THA; (v) surgery for neoplastic disease or imminently scheduled surgery and unavailable to complete the study procedures (e.g., bone tumor surgical operation); and (vi) planning another THA or total knee replacement within 6 months.

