#### Intervention structure and content

Challenges to successful post-THA functional achievement were identified, and strategies to address them were developed and integrated to design the intervention. Telephone interview was selected as the primary basis for the intervention because it is a low-cost, wide-coverage mechanism that can provide support intervention after THA for patients with limited mobility and transport difficulties [37]. Although this format has not been thoroughly investigated in patients with THA, it has been well-studied for patients with other conditions and used alone or in combination with face-to-face educational sessions and print materials [38, 39]. The initial intervention was further refined following a pilot pretest involving five patients.

The final intervention protocol includes a total of five sessions: 1 h of face-to-face education before discharge, and four additional sessions post-discharge between 1 and 6 months after surgery. Except for the hospital visit, all visits are telephone-based. The first call is approximately 40 min, with follow-up contacts ranging from 20 to 30 min. The intervention aims to enhance exercise adherence through the implementation of self-efficacy-enhancing strategies.

The initial face-to-face intervention is conducted in the hospital office before patients are discharged from the hospital after THA surgery. The focus of the initial session is to assess the functional exercise status and psychological condition of each individual, including the level of pain, the occurrence of complications, and knowledge of functional exercise. The nurse provides participants with the Rehabilitation Handbook after THA and instructs them to read it. The manual is used to supplement the face-to-face educational session. Participants are encouraged to refer to the manual at home for information. The nurses also provide video recordings of functional exercise after THA and teach patients the functional exercise movements and matters needing attention in daily life after surgery, as well as persuading and encouraging participants to set rehabilitation goals to be achieved 1 month post-THA, and mobilizing the encouragement and support of the participant’s family members.

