### Assessment of outcomes

All assessment sessions (baseline [time 1], 1 month [time 2], 3 months [time 3], and 6 months [time 4] postsurgery) include measurement of the primary and secondary outcomes. A series of questionnaires related to health outcomes of the SEEI is implemented. During the baseline assessment, additional demographic information including health, medical history, and general health status is collected.

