### Randomization and blinding

After completing all baseline data collection measures, participants are randomly divided into the intervention and control groups using computer-generated random numbers. Participants are assigned a series of continuous integers in the order of admission. To hide randomization, the independent researcher has prepared consecutively numbered, sealed, opaque envelopes, which are kept in a locked location. To avoid affecting exercise adherence behavior, participants are not informed of the two separate studies, re-randomization into this trial, or the exact details of the intervention. This process ensures adequate concealment, limiting the possibility of selection deviation. The statistician will be blinded to group allocation, which will be revealed upon completion of the statistical analyses.

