### Data analysis

IBM SPSS 25.0 will be used to analyze the collected data, according to the intent-to-treat principle. An alpha level of 0.05 will be applied for all statistical tests, and a 95% confidence interval used for all estimated values. Missing data will be managed using the last-observation-carried-forward method; this imputation method replaces missing values in the post-baseline follow-up with the last observed value for each individual. Descriptive statistics and frequency distributions will be generated for patient demographic and disease-related characteristics. Independent *t* tests and *χ*^2^ analyses will be performed to evaluate whether there are significant differences in demographic or clinical characteristics and baseline measures between the control and intervention groups. A repeated measures multivariate analysis of variance will be used to test the effects of group assignments (intervention vs. control), time (pretest vs. posttests), and group by time interaction, for the four outcome measures. If the assumption of sphericity is not met, the degrees of freedom for the *F* ratio will be adjusted according to Greenhouse-Gessler epsilon. *P*-values < 0.05 will be considered statistically significant for all comparisons.

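### The repeated-measures MANOVA uses the pre-randomisation baseline as an outcome time point instead of a covariate, so the group main effect is three quarters of the mean follow-up effect and power is lost

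*Protocol article*

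**What the plan says.** The Data analysis section of the protocol article names one model for the outcomes: "A repeated measures multivariate analysis of variance will be used to test the effects of group assignments (intervention vs. control), time (pretest vs. posttests"). The same sentence runs on to the interaction: "time (pretest vs. posttests), and group by time interaction, for the four outcome measures". The pretest is thus a level of the time factor. Baseline values are otherwise mentioned only for between-group significance tests; no covariate adjustment is named. The section does not say whether the main effect or the interaction decides.

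Under Assessment of outcomes, the sessions at baseline and at 1, 3 and 6 months "include measurement of the primary and secondary outcomes". Under Randomization and blinding: "After completing all baseline data collection measures, participants are randomly divided into the intervention and control groups".

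The primary hypothesis, at the end of the Background, is directional: adherence to the home programme over the 6 months after surgery will be higher with the intervention.

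**The concern.** Randomisation comes after the baseline measurements, so the true group difference at baseline is zero by design. A main effect that averages over all four visits mixes that known zero with the three visits that carry information about treatment. The interaction avoids this, but it asks only whether the group difference varies across visits. A significant result could come from any pattern, in either direction, and it yields no single estimate.

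Neither test therefore delivers the quantity in the primary hypothesis. Both also forgo the precision that the baseline score offers as a covariate, although that score is already collected. At stake are avoidable loss of power and a primary result that cannot be stated as one difference with a confidence interval.

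**Working it through.** **The plan's own figure.** The sample size section gives 64 per group and 150 recruited at 15% withdrawal. Check: 128 / 0.85 = 150.6, so the inflation reproduces to within one patient. The 64 cannot be derived from stated inputs, because no effect size, SD or power is given. It agrees with a two-sided 5% t test for a 0.5 SD difference (power 80.1%). I use 0.5 SD on that ground, as an assumption.

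**Inputs.**
- From the protocol: n = 64 per arm, alpha 0.05, four visits, baseline before randomisation.
- Assumed: two-sided tests, unit variances, compound symmetry with correlation ρ = 0.3, 0.5 or 0.7. The group differences (baseline, 1, 3, 6 months) are either constant (0, 0.5, 0.5, 0.5) or rising (0, 0.17, 0.33, 0.50; computed as 1/6, 1/3, 1/2).

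**Dilution.** Main effect = (0 + δ1 + δ3 + δ6) / 4 = 3/4 × the mean of δ1, δ3 and δ6. Constant profile: 0.5 becomes 0.375. Rising profile: 0.333 becomes 0.25. This holds whatever the correlation.

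**Power formulas** (noncentral F; n/2 = 32):
- Main effect: λ = 32 × Δ² / [(1 + 3ρ)/4], on 1 and 126 df, with Δ the four-visit mean difference.
- Interaction: λ = 32 × Σ(δj − mean δ)² / (1 − ρ), on 3 and 124 df, summing over all four visits.
- Baseline-adjusted mean of the three follow-ups: λ = 32 × Δ² / [(1 + 2ρ)/3 − ρ²], on 1 and 125 df, with Δ the follow-up mean difference.

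**Worked at ρ = 0.5.**
- Constant: main effect 32 × 0.375² / 0.625 = 7.2, power 76%; interaction 32 × 0.1875 / 0.5 = 12.0, power 83%; adjusted mean 32 × 0.5² / 0.4167 = 19.2, power 99%.
- Rising: main effect 32 × 0.25² / 0.625 = 3.2, power 43%; interaction 32 × 0.1389 / 0.5 = 8.89, power 69%; adjusted mean 32 × 0.333² / 0.4167 = 8.53, power 83%.

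**All scenarios, power at ρ = 0.3 / 0.5 / 0.7:**

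| Test | Constant 0.5 SD | Rising to 0.5 SD |
|---|---|---|
| Main effect, baseline as a level | 86 / 76 / 67% | 53 / 43 / 36% |
| Group by time, 3 df | 67 / 83 / 97% | 53 / 69 / 90% |
| Adjusted mean of three follow-ups | 99 / 99 / 99.9% | 80 / 83 / 92% |
| Adjusted 6-month comparison | 84 / 90 / 98% | 84 / 90 / 98% |

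The protocol also mentions a sphericity correction, which points to the univariate route. Before any correction, that route gives nearly the same interaction power at ρ = 0.5: 84% (constant) and 70% (rising).

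**Compliance, if its baseline is unrelated to later scores** (baseline correlation 0; correlation between follow-up visits 0.3 / 0.5 / 0.7):

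| Test | Constant | Rising |
|---|---|---|
| Main effect, baseline as a level | 94 / 89 / 84% | 64 / 56 / 50% |
| Group by time, 3 df | 45 / 41 / 38% | 42 / 48 / 63% |
| Follow-up visits only, averaged | 97 / 93 / 88% | 73 / 63 / 55% |

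**The case against.** The strongest defence is that, with baseline as a time level, the group by time interaction carries the treatment effect, and a zero baseline difference does not attenuate it. The analysis is valid, only less efficient. That stands: a reader might infer that both planned tests are diluted, and only the main effect is. The gain over the interaction also depends on an unstated correlation and is small at 0.7 (97% against 99.9% for a constant effect, 90% against 92% for a rising one).

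Choosing 6 months alone as the primary contrast would not clearly help either. With a constant effect and correlation 0.3 it has 84%, slightly below the planned main effect's 86%, and the hypothesis concerns the whole 6 months.

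Some stronger readings are tempting but not supported:
- **Compliance has no meaningful baseline.** Setting and population says "Patients on the surgical waiting list for THA will be invited to participate in the study after preoperative assessment", which points to a pre-operative baseline, whereas the abstract has patients recruited after surgery. The scale's items are not shown, and the four outcome measures in the model are not named. The point holds only conditionally.
- **The month-1 visit precedes the intervention.** The telephone part is described as "four additional sessions post-discharge between 1 and 6 months after surgery", but a one-hour face-to-face session takes place before discharge.
- **The method forces last observation carried forward.** The protocol gives no such link; it is a separate choice.
- **Baseline significance tests drive decisions.** Nothing makes any later step depend on them.

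**Conclusion.** The point holds as one of efficiency and of alignment with the hypothesis; it does not make the trial invalid. Two parts need no assumption about correlation or effect size: the main effect is 3/4 of the mean follow-up effect, and the interaction gives no direction or size. The power loss rests on assumed effects and correlations. Under compound symmetry, the adjusted follow-up mean exceeds the planned main effect by 13 to 33 percentage points with a constant effect and by 27 to 56 with a rising one. It exceeds the interaction by 2 to 32 points across both profiles.

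For compliance the case is weaker. If its baseline carries no information, a follow-up-only average gains 3 to 9 points on the main effect. It beats the interaction in every case shown except the rising profile at correlation 0.7 (55% against 63%). The reason to exclude a pre-operative compliance score is mainly that it cannot measure adherence after surgery.

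**What to change.** In Data analysis, replace the model with one that takes the 1-, 3- and 6-month scores as outcomes, with group, visit, group by visit and the baseline score as a covariate. Name the group difference averaged over the three follow-ups, with its 95% CI, as the primary contrast, to match the hypothesis. Report the 6-month difference as well.

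Reconcile the abstract with Setting and population on whether recruitment and baseline fall before or after surgery. If the compliance baseline is taken before surgery, analyse that scale on the follow-up visits only.

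The cost is a change of analysis wording, using data already collected. The downside is that the averaged contrast is less powerful than a 6-month contrast if the effect emerges late: 80/83/92% against 84/90/98% under the rising profile.

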### Monitoring

The trial coordinator and lead investigators meet every 2 weeks to monitor adverse events and any issues relating to the trial and to review recruitment and trial progress.

## Discussion

This study protocol describes the theoretical basis and design of an ongoing randomized controlled trial that will test the effectiveness of a patient SEEI on THA functional outcomes. THA is a common and widely accepted treatment for advanced hip arthritis, and maximum improvement of joint function is a top priority. If effective, such interventions have great potential for dissemination. In addition to their potential to enhance patient rehabilitation self-efficacy, the lessons learned in this trial can provide guidance for tailored rehabilitation strategies after THA, including family activities and exercise programs.

### Limitations

The authors acknowledge the following limitations: this is a single-center trial with no cost-effectiveness analysis and limited patient and public involvement in the design of the intervention.

## Data Availability

Not applicable.

## Abbreviations

C-HADS: Chinese version of the Hospital Anxiety and Depression Scale
HHS: Harris Hip Score
QOL: Quality of life
SCT: Social cognitive theory
SEEI: Self-efficacy-enhancing intervention
SER: Self-efficacy for rehabilitation
THA: Total hip arthroplasty
WHO-DAS II: World Health Organization Disability Assessment Schedule II
